## Abstract

**Background:**

Major depression (MDE) is prevalent in men and affects men’s health and productivity. Because of the stigma against depression and social/gender norms, men are less likely to seek help for emotion and stress-related issues. Therefore, innovative solutions tailored for men are needed. With rapid development of the Internet and information technologies, one promising solution that has drawn considerable attentions is electronic mental (e-mental) health programs and services.

**Objective:**

The objective of our study is to evaluate the effectiveness of the e-mental health program BroHealth on reducing the risk of having MDE and improving productivity and return to investment.

**Methods:**

The target population is Canadian working men who are at high risk of having MDE (N=1200). Participants will be recruited using the method of random digit dialing across the country and workplace advertisement. Eligible participants will be randomly allocated into the following groups: (1) a control group, (2) a group receiving BroHealth only, and (3) a group receiving BroHealth and telephone-based job coaching service. The groups will be assessed at 6 and 12 months after randomization. The primary outcome is the risk proportion of MDE over 12 months, which will be assessed by the World Health Organization's (WHO’s) Composite International Diagnostic Interview-Short Form for Major Depression. Intention-to-treat principle will be used in the analysis. The 12-month proportions of MDE in the groups will be estimated and compared. Logistic regression modeling will be used to examine the effect of the intervention on the outcome, controlling for the effects of baseline confounders.

**Results:**

It is anticipated that the randomized controlled trial (RCT) will be completed by 2018. This study has been approved by the Conjoint Health Research Ethics Review Board of the University of Calgary. The trial is funded by a team grant from the Movember Foundation, a global charity for men’s health. BroHealth was developed at the Digital Emergency Medicine, University of British Columbia, and the usability testing has been completed.

**Conclusions:**

BroHealth was developed based on men’s needs. We hypothesized that BroHealth will be an effective, acceptable, and sustainable product for early prevention of MDE in workplaces.

**ClinicalTrial:**

Clinicaltrials.gov NCT02777112; https://clinicaltrials.gov/ct2/show/NCT02777112 (Archived by WebCite at http://www.webcitation.org/6lbOQpiCG)

## Introduction

### Background

Major depression (MDE) affects workers’ health and productivity. In the United States, workers with depression cost an estimated US $44.01 billion per year in lost productivity [1]. One of the severe consequences of having MDE is suicide and Canadian national data showed that 76% of all suicides in 2009 were male [2]. Compounding men’s risk, men are less likely than women to seek help and to disclose depressive symptoms and often delay help seeking until symptoms become severe. If they do seek help, men are often worried about anonymity and prefer flexible and timely access. Men are socialized to be emotionally stoic and exemplify traditional masculine characteristics such as independence, self-reliance, and dominance [3]. Men are concerned over the perceived negative judgments from family and friends if they access treatment for depression. These gender-specific experiences along with a limited knowledge base about effective interventions call for innovative solutions tailored for men. With rapid development of the Internet and information technologies, one promising solution that has drawn considerable attentions is electronic mental (e-mental) health programs and services.

E-mental health is “the use of information and communication technologies to support and improve mental health, including the use of online resources, social media, and smartphone applications” [4]. E-mental health programs offer information about mental health or therapeutic services remotely through the Internet or by telephone. The increasing availability of fast broadband access provide e-mental health programs several advantages including easy and flexible access to services in remote areas and low costs. To a certain extent, e-mental health programs are closely aligned with men’s needs in terms of privacy protection, flexible, and timely access to help. There have been a number of e-mental health programs for therapeutic intervention. A recent review by Christensen and Petrie showed that by 2013 there had been 62 Web-based mental health interventions and 11 mobile apps [5]. Lal and Adair found 91 peer-reviewed publications on the application of e-mental health interventions between 2000 and 2010 [6]. However, the number of randomized controlled trials (RCT) has not been proportionate to the number of e-mental health programs. For example, only 30.1% of the 73 programs identified in Christensen and Petrie's review had been evaluated by one or more RCTs [5]. Many of the existing e-mental health programs for depression were developed based on the approach of cognitive behavioral therapy (CBT). The most widely disseminated e-mental health program based on CBT is MoodGYM developed in Australia [7]. Other well-known e-mental health programs for depression that have been evaluated by at least one RCT include Sadness [8], e-couch [9], BluePages [7], and myCompass [10]. Although e-mental health programs offer a non-threatening, convenient, and anonymous environment, some users reported that going through the CBT sessions and exercises were laborious, the sessions were not relevant with the users’ unique personal issues, and there was a lack of personal interaction [11]. Our research project, BroMatters, intends to overcome these limitations.

BroMatters is a project aiming to develop and evaluate an e-mental health program for early prevention of major depression in Canadian male workers who do not have MDE, but are at high risk. It is a collaboration among researchers and stakeholders from five Canadian universities and six national and local non-government organizations (NGOs). To develop the e-mental health program, BroMatters conducted a national survey in male workers who did not have MDE, but were at high risk, to understand their preferences of design features of e-mental health programs [12]. Informed by the survey results, the BroMatters team developed an e-mental health program (BroHealth) to be evaluated by a RCT.

### Objectives and Hypotheses

The primary objective of the proposed RCT is to evaluate the impacts of BroHealth and telephone-based job coaching on the risk of MDE among Canadian male workers who are at high risk of having MDE. We hypothesized that the 12-month risk proportion of MDE in the intervention group will be lower than that in the control group.

The secondary objectives of the proposed RCT are to (1) evaluate the impacts of BroHealth and telephone-based job coaching on changes in depression, anxiety, absenteeism and presenteeism, return on investment, and predicted MDE risk; and (2) compare participants who receive BroHealth only and those who receive both BroHealth and telephone-based job coaching services in changes in depression, anxiety, absenteeism and presenteeism, return on investment, and predicted MDE risk.

## Methods

### Study Design

The proposed mixed-methods study is a prospective, intention-to-treat, RCT with the following 3 arms: (1) control group (n=400) that will receive general information about men’s mental health (the Movember Foundation website on men’s mental health), (2) intervention arm 1 group (n=400) that will receive the e-mental health program, and (3) intervention arm 2 group (n=400) that will receive the e-mental health program, and telephone-based interactive work-life coaching.

An embedded qualitative interview component will be conducted with a sub sample of participants from the intervention groups to obtain in-depth perspectives about the effectiveness of interventions at the 12-month endpoint. A flow chart of the proposed trial based on the Consolidated Standards of Reporting Trials (CONSORT) criteria is shown in Figure 1.

**Figure 1 figure1:**
[figure not shown]
BroMatters clinical trial flow diagram.

### Study Setting and Inclusion Criteria

Eligible participants will be recruited from 10 provinces of Canada. Recruitment and fully structured baseline interviews will be conducted by Leger, a Canadian-owned polling and research firm; follow-up interviews will be conducted at the telephone interview laboratory of the Mathison Centre for Mental Health and Education, University of Calgary. The proposed trial will target Canadian male workers who are aged 18 years or older, are working for pay at the time of recruitment, and at the time of recruitment and baseline assessment, are not experiencing a MDE, but have a high risk of having MDE based on our prediction algorithm. Since it was found that 20% of Canadian adult men had a probability of 6.51% or higher in terms of the predicted MDE risk [13], for the proposed study, a personalized risk (or probability) of 6.51% or higher will be defined as high risk for men. In addition, the trial will target workers who may have had MDE in the past 12 months, but are in remission for at least 2 months prior to the study, have no language barriers to English or French, have access to the Internet for personal use, and can provide email and mailing addresses.

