### Outcomes and Measurements

#### Primary Outcome

The primary outcome is the 12-month risk proportion of MDE, which is the WHO’s Composite International Diagnostic Interview-Short Form (CIDI-SF) [16], will be administered to determine MDE in the past 12 months, based on the Diagnostic and Statistical Manual of Mental Disorders (DSM) criteria [17]. The Composite International Diagnostic Interview-Short Form for Major Depression (CIDI-SFMD) is a structured diagnostic interview for MDE, which has been repeatedly incorporated, without modification, into a series of national health surveys by Statistics Canada, starting in 1994. The CIDI-SFMD was developed from the full version of CIDI to provide a quick screen of MDE [16]. The WHO’s CIDI has been widely used in population-based mental health surveys in different countries. MDE represents a purported 90% predictive cut point for the CIDI-SFMD. Using the full CIDI diagnosis as “gold standard”, the sensitivity and specificity of the CIDI-SFMD was 89.6% and 93.9%, respectively [16].

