### Recruitment and Screening

Recruitment and screening will be contracted to Leger that has access to the numbers of household landlines and mobile phones across the country. Recruitment will be conducted using the method of Random Digit Dialing (RDD). Once a potentially eligible participant is identified, the interviewer will confirm the participant’s age, working status, and access to the Internet for personal use, by asking “Do you have access to Internet for personal use, through computer or mobile device?” Then the CIDI-SFMD [16] will be administered. This is to assess MDE in the past 12 months and to ensure the participant is not experiencing a MDE at the time of interview.

If a participant has had MDE in the past 12 months, he will be asked “In the past 2 months or longer, has your mood been much improved or back to normal AND you DIDN’T have any symptom of (key phrases)?” Those who answer “no” will be excluded.

Following this, the sex-specific prediction algorithm for MDE will be administered. The algorithm for men contains 15 questions about personal and family history of MDE, current health status, childhood trauma, and recent negative life events [13]. With the input of the answers to these questions, the algorithm generates the participant’s probability of having MDE in the next 4 years. The original development analysis showed that a probability of 6.51% represented the top 20% of Canadian adult men in terms of the risk of having MDE [13]. In this study, those who have a risk less than 6.51% are considered being at low risk and will be excluded from the study.

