### Follow-Up Assessments

The post-randomization assessments will be conducted at 6 and 12 months. At the 6- and 12-month assessments, information regarding demographic and occupational characteristics questions, including changes in marital status and employment, alcohol use, self-rated physical health, CIDI-SFMD, PHQ-9 for depression, GAD-7 for anxiety, WHO’s HPQ, sleep disturbance, anger, quality of life, and mental health service will be collected.

It is anticipated that time is needed to schedule follow-up interviews and there will be conflicts with scheduled interviews (eg, some participants may have to cancel a scheduled interview, or some do not respond to a scheduled phone call). Therefore, a 2-month interview window will be allowed for each follow-up interview.

To obtain in-depth information about how BroHealth affects men’s behaviors and risk profile, qualitative interviews will be conducted via telephone with 10% of the participants in the intervention groups at the end of the RCT (ie, after the 12-month assessment). The participants will represent those with diverse outcomes (clinical and occupational trajectories, and employment status changes). Qualitative interview data will yield in-depth data about the impacts of receiving BroHealth and job coaching on the outcomes. These data will be used to support and interpret the primary quantitative data base. The multiple forms of evidence generated through mixed methods designs are particularly useful for illuminating complex health issues [26].

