### Statistical Analysis

All data analyses will be conducted using the most recent version of STATA. An Intention-to-treat (ITT) principle will be used in the analysis (eg, initial intervention assignment rather than intervention received will be used in the analysis).

For the primary objective, the proportions of MDE over 12 months will be estimated for each group and will be compared using chi-square tests between control versus intervention #1, and control versus intervention #2. Logistic regression modeling will be used to examine the effect of the intervention on the outcome, controlling for the effects of baseline confounders. Contrast analysis will be conducted to compare different intervention groups (intervention #1 vs intervention #2) as one of the secondary objectives.

For the secondary objectives, the distributions of the changes in the depression and anxiety scores at 6 and 12 months in the intervention and control groups will be examined. The means of the changes between the intervention and control groups will be compared using *t* tests.

If the assumption of normal distribution is violated, transformation or non-parametric testing will be used. Analysis of variance (ANOVA) will be conducted to examine between group differences (separately for the 6- and 12-month assessments), controlling for the effects of baseline characteristics. Repeated-measures mixed models will be used to examine intervention effect (time x intervention), controlling for the effects of baseline characteristics. The analyses will be repeated for absenteeism and presenteeism (secondary objectives).

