## Discussion

### Principal Findings

BroHealth is novel in several ways. First, BroHealth focuses on early prevention of major depression, rather than providing treatment to those who already have MDE. The outcomes include not only reduced risk of MDE, but also improved work functioning, productivity, and return on investment. Second, BroHealth was developed through a gender lens, focusing on the working men who are at high risk of having MDE. Third, the development of BroHealth was informed by men’s preferences of design features of e-mental health programs, through a national survey of the target population. To this extent, this approach enhances the acceptability of BroHealth by working men who are at high risk of MDE.

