### Limitations

BroHealth was designed to be used by male workers who have access to the Internet. Men who don’t have Internet access for personal use will not be included. Some elements of BroHealth were based upon existing programs. For example, the CBT program of BroHealth was adapted from the abbreviated version of the UK Living Life to the Full (LLTTF), and the mindfulness relaxation program was developed by University Health Network in Ontario. However, the French materials for the mindfulness relaxation program were not available. This may affect the effectiveness of BroHealth in French speaking participants. We will examine this potential impact by conducting the proposed analyses in English and French speaking participants separately. The incidence of MDE will be measured by CIDI-SF for MDE, which is a fully structured diagnostic interview, rather than by physician diagnosis. Therefore, misclassification of diagnosis is possible.

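### The crude primary chi-square ignores past-12-month MDE, a likely strong predictor that screening already records; stratify on it and report both groups

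*Protocol article*

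**What the plan says.** All references are to the protocol article.

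- **Entry (Study Setting and Inclusion Criteria).** Men must not be in an episode and must have a predicted risk of at least 6.51%. The section also says that "the trial will target workers who may have had MDE in the past 12 months, but are in remission for at least 2 months".
- **Screening (Recruitment and Screening).** The CIDI-SFMD is given to each potential participant. "If a participant has had MDE in the past 12 months, he will be asked" about the last 2 months, and only a negative answer excludes him. A yes/no record of MDE in the past year therefore exists for every man before randomization. The risk algorithm contains "15 questions about personal and family history of MDE, current health status, childhood trauma, and recent negative life events".
- **Outcome (Primary Outcome).** The CIDI-SF "will be administered to determine MDE in the past 12 months". Recurrence and new onset are not separated.
- **Randomization.** One sorted list of 1200 numbers is cut into three groups of 400, without strata.
- **Analysis (Statistical Analysis).** The 12-month proportions "will be compared using chi-square tests between control versus intervention #1, and control versus intervention #2". A logistic model adjusting for baseline confounders is also planned; its covariates are not named.
- **Wording.** Limitations says that "The incidence of MDE will be measured by CIDI-SF for MDE". Principal Findings says that "BroHealth focuses on early prevention of major depression, rather than providing treatment to those who already have MDE". The only separate analysis announced is by language (Limitations).

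**The concern.** The entry rule combines men with no MDE in the past year and men who may be only two months out of an episode. If the second group has a clearly higher 12-month risk, a modest share of the sample can supply a large share of the events. Three things follow.

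1. The crude chi-square leaves a measured source of outcome variation unused, so some precision is lost.
2. With unstratified allocation, a chance difference between arms in the share of recently ill men passes straight into the crude risk difference. The planned difference is only 3.1 percentage points, so a shift of one point matters.
3. A single pooled proportion per arm does not show whether a benefit arose in men with or without a recent episode. Readers of a prevention trial will ask this, and the data to describe it are already collected.

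**Working it through.** **Plan's own figure.** Inputs from Sample Size Calculation: 3.9% control, 0.8% intervention, two-sided alpha 0.05, power 0.80.

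n = [1.96·√(2p̄(1−p̄)) + 0.8416·√(p₁(1−p₁)+p₂(1−p₂))]² / (p₁−p₂)², with p̄ = 0.0235.

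n = (0.4199 + 0.1794)² / 0.031² = 373.7, so 374 per arm. This reproduces the stated figure. Power at 400 per arm is 82.6%. The calculation treats the sample as one population.

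**Assumed inputs.** The documents give no share of recent-episode men (s), no recurrence rate in them (r) and no effect on recurrence. I take s = 10-30%, r = 15-30%, and 3.9% (0.8% on intervention) in other men.

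**Share of control events from recent-episode men** = s·r / [s·r + (1−s)·0.039].

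| s | r = 15% | r = 30% |
|---|---|---|
| 10% | 0.0150/0.0501 = 30% | 0.0300/0.0651 = 46% |
| 20% | 0.0300/0.0612 = 49% | 0.0600/0.0912 = 66% |
| 30% | 0.0450/0.0723 = 62% | 0.0900/0.1173 = 77% |

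**Chance imbalance.** The 95% range for the difference in share between two arms of 400 is ±1.96·√(2s(1−s)/400): ±4.2 points at s = 10% and ±6.4 points at s = 30%. Multiplying by the risk gap (r − 3.9%) gives the shift in the crude risk difference:

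- s = 10%, r = 20%: 4.2 × 0.161 = about 0.7 points.
- s = 30%, r = 30%: 6.4 × 0.261 = about 1.7 points.

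Both compare with a planned effect of 3.9 − 0.8 = 3.1 points.

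**Power, crude chi-square against Mantel-Haenszel (normal approximation), 400 per arm.** Three cases for recurrence: the same relative risk as in other men (0.8/3.9 = 0.205), half that relative reduction, and no effect.

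| s, r | same | half | none |
|---|---|---|---|
| 10%, 20% | 93% → 94% | 77% → 79% | 51% → 54% |
| 10%, 30% | 97% → 98% | 78% → 82% | 43% → 49% |
| 30%, 30% | 99.9% → 100% | 82% → 87% | 17% → 19% |

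Over s = 10-30% and r = 15-30% the gain is about 0 to 6 points, never a loss. Widening to s = 5-30% and r = 10-40% raises the upper end to about 9 points.

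**What the pooled figure hides.** Take s = 20%, r = 20%, so pooled control is 0.8 × 3.9% + 0.2 × 20% = 7.1%.

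- Effect only in men without a recent episode: the pooled difference is 0.8 × 3.1 = 2.5 points.
- Effect only in recent-episode men (relative risk 0.205, so 20% falls to 4.1%): the pooled difference is 0.2 × 15.9 = 3.2 points.

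The two pooled results are close, and only the stratum proportions tell them apart.

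**The case against.** **The protocol does not contradict itself.** Its stated target is the risk of MDE in working men at high risk. Personal history of MDE is one of the algorithm's inputs, so previously ill men belong to the intended population. Men in remission do not currently have MDE, so the contrast between prevention and treatment is respected. First onset is never claimed, and the word incidence describes the outcome once, in a sentence about misclassification. This stands. A reader might infer that the trial promises to prevent first episodes and then tests something else; the text does not support that.

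**Adjustment is already planned.** The logistic model could include past-12-month MDE, and covariate lists are commonly left to an analysis plan. An unnamed covariate is therefore no fault. But the crude chi-square is stated in the article for the primary comparisons, and an adjusted model with one pooled effect would still not show results by recent-episode status.

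**Pooling is not bias.** Correct. Randomization makes the crude test valid, and its type I error already allows for chance imbalance. What remains is precision and interpretability.

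**The sizes are assumed.** Also correct. A reader might infer that a small recently ill group would supply most events. At a 10% share with the 3.9% planning rate it supplies 30-46%, which is less than half.

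**Restricting the prevention claim to men without a recent episode would not work.** That stratum still contains men whose last episode was more than 12 months ago. At the planning rates, removing 10, 20 or 30% of men leaves 360, 320 or 280 per arm, and power falls from about 83% to 79, 74 or 68%, before attrition. This objection stands in full.

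**Conclusion.** The point holds as one of precision and interpretation. The primary comparison pools men with and without MDE in the past year and uses a crude test, although the status is known for every man before randomization.

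On the assumed inputs, recent-episode men supply about 30-77% of control events. Chance imbalance can move the crude difference by about 0.7 to 1.7 points in the two cases shown, against a planned 3.1. Stratifying gains about 0 to 6 points of power. All of this rests on assumed shares and recurrence rates. That a recent episode is a strong predictor is likely, but the documents do not show it.

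Two stronger readings should not be drawn. The entry rule does not invalidate the trial or contradict its aim. Nor do the documents show that entry episodes will be counted as outcomes. It is true that "The post-randomization assessments will be conducted at 6 and 12 months" and that the instrument looks back 12 months, so the recall at 6 months reaches before randomization. But the Randomization section counts what occurs after randomization, and how onset is dated is a detail that an article may leave out.

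**What to change.** Leave eligibility, randomization and data collection as they are, and keep the full intention-to-treat population and the pooled primary conclusion.

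- **Statistical Analysis, primary objective:** replace each crude chi-square against control with a Mantel-Haenszel test and Mantel-Haenszel risk difference, stratified by past-12-month MDE (yes/no) from the screening CIDI-SFMD. Name the same variable as a covariate in the logistic model.
- **Same section:** state that 12-month MDE proportions and risk differences will be given in both strata, descriptively and without separate claims.
- **Limitations:** describe the outcome as the risk of an MDE over 12 months instead of incidence.

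The prevention claim should stay on the whole randomized population. The change should be fixed before group status is linked to the interview data; after that, the stratum results would be post hoc.

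The cost is a little more analysis and imprecise stratum estimates. At a 10% share, for example, the recent-episode stratum has about 40 men per arm. The other stratum, with 360 per arm, would have about 14 control events (360 × 0.039) and 3 intervention events (360 × 0.008).
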